### Measurements

Primary outcome measures of the randomised trial was BMI(sds). Secondary outcome measures were glucose tolerance, dietary behaviour, physical activity, sedentary behaviour and self-esteem. Data were collected at baseline and after 6 and 18 months intervention. All measurements were performed after an overnight fast, except for the dual energy x-ray absorptiometry (DEXA).

### - Body composition

#### Height, weight and waist circumference

Height was measured and recorded with an accuracy of 1 mm with a electronic stadiometer (KERN 250D). Body weight was measured (in underwear) and recorded within 0.1 kg with a calibrated electronic flat scale (SECA 861). Weight and height were used to calculate BMI (weight in kilograms divided by the square of height in meters). The degree of overweight was quantified using Cole's least mean square method, which normalized the BMI's skewed distribution and expressed BMI as BMIsds [15]. Reference data of Dutch children were used (; versie 3.5). The BMIsds indicates how many standard deviations a measurement is above or below the median of the distribution.

#### Bio-electrical impedance spectroscopy

After an overnight fast, bio-electrical impedance spectroscopy (BIS) measurements were performed at the non-dominant side of the subject, using a Hydra ECF/ICF Bio-Impedance Spectrum Analyzer, model 4200 (Xitron Technologies, San Diego, CA, USA). Shoes and socks were removed and the subjects were in a supine position. Two current electrodes (tetra-polar electrodes (3 M red Dot AG/AgCl)) were placed at the dorsal surfaces of the hand and foot on the distal portion of the second metacarpal and metatarsal, respectively. Two detector electrodes were placed at the posterior wrist between the styloid processes of the radius and ulna and at the anterior ankle between the tibial and fibular malleoli. The resistance and reactance measured at 50 kHz were used in the analysis, obtained by the program Hydra Data Acquisition Utility. With this technique, two body compartments, fat mass (FM)) and fat free mass (FFM), can be determined.

#### Dual energy x-ray absorptiometry

Subjects were scanned for 10 minutes in underwear while lying in supine position with arms and legs abducted from the body. All measurements were whole body scans performed with a Hologic QDR-Delphi, S/N 45665. The DXA method measures three components of the body: bone mineral content (BMC), fat mass (FM) and lean tissue mass (LTM). These components were calculated based on the differential attenuations of the two photon beams, caused by the differences in density and chemical composition [22,23].

### Energy expenditure

Resting oxygen consumption (VO_2_), and carbon dioxide production (VCO_2_) were measured by O_2_, CO_2 _flow with a ventilated hood system for 30 minutes with a metabolic monitor (Vmax Encore n29, Viasys Healthcare, Houten, The Netherlands) after an overnight fast. Before each test, the gas analysers were calibrated with two reference gas mixtures (16% O_2_, 4% CO_2 _and 26% O_2 _(Viasys)). The subjects were monitored during the measurements to prevent any movement or sleeping under the hood. The first 5 minutes were excluded to account for environment adjustment by the children and gas adaptation in the hood. Then resting energy expenditure (REE) was calculated from oxygen consumption and carbon dioxide production by using the equation of Weir [24].

### Metabolic measurement

#### - Glucose tolerance and insulin resistance (Oral Glucose Tolerance Test)

After an overnight fast subjects were given glucose, in a dose of 1.75 g per kilogram of body weight (up to maximum of 75 g) orally, and blood samples are obtained after 0, 30 and 120 minutes for the measurement of plasma glucose and insulin levels. Impaired glucose tolerance was defined, according to the American Diabetes Association guidelines, as a fasting plasma glucose level between 5.6 – 6.9 mmol/l and a two-hour plasma glucose level between 7.8–11.1 mmol/l. Type 2 diabetes was defined as a fasting glucose level of 7.0 mmol/l or higher or a two-hour plasma glucose level of more than 11.1 mmol/l [25].

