## Background

Overweight and obesity in childhood are associated with negative psychosocial factors, orthopaedic complications, an increased risk for diseases such as hypertension, dyslipidaemia, asthma, sleep-apnoea and a strong increase of impaired glucose tolerance [1,2]. Impaired glucose tolerance precedes the onset of type 2 diabetes mellitus [3]. Overweight children are likely to remain overweight and are at increased risk of becoming obese compared to children of normal weight [4].

Sinha and co-workers found impaired glucose tolerance in 21% of obese children and 25% of obese adolescents [3]. Four percent of these obese adolescents had type 2 diabetes. At the paediatric outpatient clinic of the VU University Medical Center, glucose-intolerance and insulin-resistance was diagnosed in 18% and 52% of obese adolescents, respectively [5]. In 2003, the last Dutch national surveillance system of diabetes in children reported the first children with type 2 diabetes as a result of obesity.

Several reviews on interventions for treating obesity in children have been produced recently. These reviews suggest that there is some evidence that treatment of obesity in children and adolescents is feasible. However, there is a limited amount of data on effective components of programs to treat childhood obesity [6-10]. Cognitive behavioural modification techniques have shown promising results regarding lifestyle changes in obese children [11]. For obese adolescents the impact of an intensive intervention programme aimed at attaining a healthy lifestyle has not yet been evaluated. The prevalence of obesity in the Netherlands is, analogous to the United States, expected to increase in the coming years [12]. Therefore, there is an urgent need for interventions aimed at the prevention of obesity among adolescents as well as effective therapeutic interventions aimed at a healthy weight of the already obese.

For this reason, we developed Go4it, an intervention program for obese adolescents. This paper describes the design of the Go4it study, a randomised controlled trial (RCT) with an economic evaluation alongside. The aim of this study is to investigate the effectiveness and cost-effectiveness of this multidisciplinary group treatment for obese adolescents.

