### Sample size calculation

The sample size calculation is based on a difference in BMIsds of 0.29 (10%) between the intervention and control group after 18 months. The standard deviation for this BMIsds is considered to be 0.5. Based on these data, in an intention-to-treat analysis, 43 subjects per group are needed to detect this difference in mean BMIsds with an alpha of .05 and a power of .80. A sample of 108 persons (n = 54 per group) is required taking into account a dropout rate of 25% [5,11].

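### Impaired glucose tolerance needs both an intermediate fasting and an intermediate two-hour value, while diabetes needs only one, so participants with one intermediate value get no label

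*Protocol article*

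**What the plan says.** The section on glucose tolerance and insulin resistance gives two definitions in adjacent sentences.

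- Impaired glucose tolerance: "a fasting plasma glucose level between 5.6 – 6.9 mmol/l and a two-hour plasma glucose level between 7.8–11.1 mmol/l". The source is named in the same sentence: "Impaired glucose tolerance was defined, according to the American Diabetes Association guidelines".
- Type 2 diabetes: "a fasting glucose level of 7.0 mmol/l or higher or a two-hour plasma glucose level of more than 11.1 mmol/l".

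The first definition joins its criteria with *and*, the second with *or*. No label is given for a participant with only one value in the intermediate range, and nothing elsewhere in the article changes either rule.

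The Measurements section gives the outcome its role: "Secondary outcome measures were glucose tolerance, dietary behaviour, physical activity, sedentary behaviour and self-esteem". The Background describes the order of the disease states: "Impaired glucose tolerance precedes the onset of type 2 diabetes mellitus".

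**The concern.** The trial is motivated by preventing type 2 diabetes, and glucose tolerance is one of its named outcomes. A category for the intermediate state should pick up participants whose glucose handling is abnormal but not yet diabetic. The rule as written picks up only those who are intermediate on both tests at once.

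Three things follow if an analyst codes the text as it stands:

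- A participant with a normal fasting value and a clearly raised two-hour value is a non-case, although the outcome is named after glucose tolerance.
- A participant whose fasting value drops from 5.6 to 5.5 mmol/l leaves the impaired category even if the two-hour value does not move.
- A participant can go from unclassified to diabetes without ever being impaired.

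Any binary comparison of the arms on this outcome would then rest on fewer cases, and on a mixture of fasting and post-load information.

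**Working it through.** There is no stated figure to reproduce, so the check has two parts: the logic of the two rules, and an illustration of how many participants the gap could involve.

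**Part 1. The rules as written**

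Let F be fasting glucose and H two-hour glucose, both in mmol/l.

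- Diabetes: F ≥ 7.0 or H > 11.1.
- Impaired: 5.6 ≤ F ≤ 6.9 and 7.8 ≤ H ≤ 11.1.
- Neither: everything else. This is the implied remainder; the article does not name it.

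| F | H | As written | If either intermediate value counts |
|---|---|---|---|
| 5.0 | 6.5 | neither | neither |
| 5.0 | 9.0 | **neither** | impaired |
| 5.0 | 11.5 | diabetes | diabetes |
| 6.0 | 6.5 | **neither** | impaired |
| 6.0 | 9.0 | impaired | impaired |
| 6.0 | 11.5 | diabetes | diabetes |
| 7.2 | 6.5, 9.0 or 11.5 | diabetes | diabetes |

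The two rows in bold are the gap. When F is below 5.6, no value of H gives the impaired label. At F = 5.0, H = 11.0 is neither and H = 11.2 is diabetes. These results follow from the wording alone and need no assumption.

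**Part 2. How many participants could be involved**

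Inputs from the article:

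- Planned sample of 108 (Sample size calculation).
- 18% glucose intolerance at the recruiting clinic (Background). The article does not say how that 18% was defined. Treating it as the share with a raised two-hour value is an assumption.

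Further assumptions, not in the article:

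- Share with a raised fasting value, p_F: 5% to 30%.
- Correlation r between the two values: 0.2 to 0.6.
- A bivariate normal model in which *raised* means above the lower limit of the intermediate range. The upper limits are ignored for simplicity.

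Expected number with a raised two-hour value: 108 × 0.18 = 19.4.

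The *and* rule keeps the joint probability P(both raised). The share captured is P(both raised) / 0.18, and the expected count is 108 × P(both raised).

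| p_F | r | P(both raised) | Share captured | Count per 108 |
|---|---|---|---|---|
| 5% | 0.2 | 0.015 | 8% | 1.6 |
| 10% | 0.4 | 0.041 | 23% | 4.4 |
| 20% | 0.6 | 0.092 | 51% | 10.0 |
| 30% | 0.4 | 0.094 | 52% | 10.2 |
| 30% | 0.6 | 0.119 | 66% | 12.8 |

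The rule therefore captures about 2 to 13 of 19. I calculated p_F = 5, 10, 20 and 30% crossed with r = 0.2, 0.4 and 0.6. Fewer than half are captured in 9 of those 12 combinations, and more than half in the other three (the last three rows above).

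**The case against.** **The *and* may be loose drafting.** In a one-sentence summary of a guideline, it could list two ranges rather than require both. This is plausible, and the guideline is not available here, so a departure from it cannot be shown. The adjacent sentence does use *or*, though, and a reader who codes the text literally builds the variable described above. The point rests on the wording, not on what the guideline says.

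**The two definitions do not contradict each other.** This stands. Every pair of values gets exactly one result, so what they leave is a gap in coverage. The Background sentence on disease order describes natural history, and a classification rule can fit it badly without contradicting it.

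**A reader might infer that most cases are lost.** The article does not support that. Every participant with *only* a raised two-hour value is left out, but how large a part of all raised two-hour values this is depends on assumed inputs. Over the assumed range the loss runs from about a third to over 90%.

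**A reader might also infer that the trial's rate cannot be compared with the clinic's 18%.** That depends on how the 18% was defined, which the Background does not say. It could rest on the same rule.

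**The planned analysis may not be binary.** The Statistical analyses section names linear and logistic regression without assigning either to glucose tolerance. A continuous, baseline-adjusted analysis is compatible with the plan and would not be touched. The concern therefore applies only to analyses or tables that use the category. Which form should be the main analysis is a matter of preference and no part of this point.

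**Conclusion.** The point holds as a defect in a stated outcome definition. Applied literally, the rule leaves every participant with a single intermediate value unlabelled and makes the impaired stage unreachable for anyone with fasting glucose below 5.6 mmol/l. That much is certain from the text.

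The size is not certain. About 2–13 of 19 captured per 108 is an illustration. It rests on reading 18% as the two-hour prevalence, 5–30% with a raised fasting value, a correlation of 0.2–0.6 and bivariate normality.

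The reach is limited. Under Measurements, glucose tolerance is secondary to BMI(sds). The abstract places its primary-outcome label beside glucose tolerance and insulin resistance, but that is a separate inconsistency and does not raise the weight of this point. The BMIsds outcome, the sample size and the continuous glucose and insulin values are unaffected. It should be corrected before any categorical glucose-tolerance result is produced.

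**What to change.** For the trial's outcome classification only:

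1. Replace the *and* rule so that an intermediate value on either test is classified.
2. Report the two-hour (post-load) category and the fasting category separately, using the ranges already in the article, so that they line up with the *or* used for diabetes. Participants intermediate on both can be shown as the overlap.
3. Check the reworded sentence against the cited guideline, and state the intended connective if the present wording was shorthand.

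The cost is one reworded definition and one extra row or column in the results. The fasting and 120-minute samples are already part of the test, so no new measurement is needed. This concerns how the outcome is labelled for analysis, not how any participant is diagnosed or managed.

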### Questionnaires

After the Oral Glucose Tolerance Test (OGTT) participants complete the following questionnaires:

#### - Dietary behaviour

Questions about two risk behaviours i.e. consumption of sugar-sweetened beverages and consumption of high-sugar/high-fat content snacks [14]. The questionnaire is based on other validated questionnaires for assessing dietary intake [26,27]. Adolescents indicate how many days a week they consume sugar-sweetened beverages or energy dense snacks, and the amount/number of servings of sugar-sweetened beverages or energy dense snacks they usually consume on these days, thinking of the last week.

#### - DEBQ: Dutch Eating Behaviour Questionnaire

Eating behaviour is assessed using the Dutch Eating Behaviour Questionnaire. This questionnaire consists of 33 items, on emotional (13 items), external, and restrained eating (both 10 items). All items are rated on a five-point scale ranging from 1 (never) to 5 (very often). The DEBQ scales have high internal consistency, high validity, and high convergent and discriminative validity [28,29].

#### - Physical activity and sedentary behaviour

The Activity Questionnaire for Adolescents & Adults (AQUAA), is based on the Short Questionnaire to Assess Health-enhancing physical activity (SQUASH)[30]. This questionnaire was not designed to asses' energy expenditure, but to give an indication of the habitual activity level and sedentary behaviour. The AQuAA questionnaire is structured in commuting activities, leisure time activities, household activities, and activities at work and school. For every item examples of activities are provided. The test-retest reliability and validity are currently being studied (Chin A Paw et al, submitted).

#### - Quality of life

##### Child Health Questionnaire (CHQ)

The 87-item questionnaire-child form is a generic health status measure covering physical and psychosocial domains and was developed specifically for children and adolescents. The 87 items with 4, 5 or 6 response options is divided over 10 multi-item scales and two single-item questions. Per scale the items are summed up and transformed into a 0 (worst possible score) to 100 (best possible score) scale [31,32].

##### Pediatric Quality of Life Inventory™ Version 4.0 (PedsQL™ 4.0)

The 23-item PedsQl ™ 4.0 Generic Core Scales for children aged 2 to 18 years encompasses:

1) physical function (8 items), 2) emotional functioning (5 items), 3) social functioning (5 items), and 4) school functioning (5 items). The instrument takes approximately 5 minutes to complete. The instructions ask how much of a problem each item has been during the pas month. A 5-point Likert response scale is utilized (0 = never a problem to 4 = almost always problem). Scales are standardized, and scores range from 0–100, with higher scores representing better quality of life. The PedsQL has been shown to be both reliable and valid [33,34].

##### Body Esteem Scale for Adolescents and Adults

The body esteem (BE) questionnaire for adolescents has 3 subscales: BE-Appearance (general feelings about appearance), BE-Weight (weight satisfaction), and BE-Attribution (evaluations attributed to others about one's body and appearance). The subscales have high internal consistency and 3 month test-retest reliability [35].

### Statistical analyses

Descriptive statistics (means ± SD, or median and interquartile ranges, as appropriate) will be used to describe the study sample with regard to baseline characteristics. To evaluate the effects of the intervention, longitudinal linear and logistic regression analysis will be used. The mean difference between intervention and control group with 95%-confidence intervals will be calculated. Regression analyses will be adjusted for baseline values and possible confounders such as gender and age. Also effect modification will be investigated using interaction terms between intervention group and gender and age, respectively. All analyses will be performed according to the intention-to-treat-principle, meaning that we will not impute values for missing data [36].

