### Intervention

Go4it is a multidisciplinary group treatment for obese children that is based on the programmes of Braet et al [11], Epstein et al [13] and the materials of the Dutch Obesity Intervention in Teenagers (DOiT) [11,14]. During 7 sessions with an interval of 2–3 weeks the adolescents received education on dietary behaviour, physical activity and energy balance. They also received cognitive behavioural therapy in which they were learned how to improve their lifestyle regarding a healthy weight and how to maintain an adequate energy balance. Go4it was carried out multidisciplinary in an outpatient clinic with a dietician, paediatrician/endocrinologist and psychologist involved. The first session was focussed on increasing awareness of the current lifestyle. Besides dietary and activity journals, step counters (pedometers) were used to increase awareness of the actual behaviour. Next, the adolescents had to set goals with respect to improving their energy balance behaviour. Additionally cognitive-behavioural therapy characteristics were used, e.g. learning to cope with difficult situations (parties, holidays) and teasing. Go4it works with homework tasks and the education is interactive. After 6, 14, 26, and 36 weeks, booster group sessions were scheduled in order to encourage the adolescents to maintain or further improve their energy balance behaviour and to discuss possible problems or questions. In addition, two separate sessions for the parents were organised. These parental sessions consisted of education concerning the health risks of overweight, healthy physical activity and dietary behaviour and how to support their children. Special materials were developed for this program; an information book, a workbook, and a dietary and activity diary. In addition, specific worksheets for every session were developed. The control group received the current regular care, consisting of referral to a dietician in the home care setting.

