### Economic evaluation

An economic evaluation will be conducted from a societal perspective. All relevant costs will be assessed, valued and analysed. Costs will include costs of the interventions (Go4it programme and usual care), but also other health care related costs. For example, costs of visits to general practitioners, psychologists, physiotherapists, dieticians, paediatricians will also be estimated as well as costs of medication. Indirect costs of production loss are not relevant in this population of teenagers. Relevant cost data will be collected through cost diaries [37]. Costs will be valued according to guidelines for economic evaluation in the Netherlands. Primary outcomes in the economic evaluation will be quality of life, BMI, physical activity and dietary behaviour. The economic evaluation will be performed according to the intention-to-treat principle. A cost-effectiveness analysis will be performed. The mean differences in total costs between intervention groups will be estimated and bootstrapping will be used to estimate 95% confidence intervals.

Cost-effectiveness ratios will be estimated using bootstrapping techniques and graphically presented on cost-effectiveness planes. The incremental cost-effectiveness ratio expresses the additional costs of the Go4it programme per unit improvement of effect. Acceptability curves will also be presented in which the probability that the programme is cost-effective is expressed as a function of willingness-to-pay.

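### Go4it is delivered in groups in one arm only, but neither the sample size nor the named analyses allow for correlation within groups; if it exists and is ignored, standard errors are too small

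*Protocol article*

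**What the plan says.** The Intervention section describes the experimental arm thus: "Go4it is a multidisciplinary group treatment for obese children". There are seven sessions at intervals of 2–3 weeks, and afterwards "booster group sessions were scheduled in order to encourage the adolescents to maintain or further improve their energy balance behaviour" (four of these, listed at 6, 14, 26 and 36 weeks). Two separate parent sessions are also mentioned. Controls are referred to a dietician in home care; no group delivery is described for them.

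The Randomisation procedure section assigns individual participants, stratified by age group and gender.

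The Sample size calculation section sets out its inputs: "The sample size calculation is based on a difference in BMIsds of 0.29 (10%) between the intervention and control group after 18 months". With an assumed SD of 0.5, it concludes that "43 subjects per group are needed to detect this difference in mean BMIsds with an alpha of .05 and a power of .80". It then allows for 25% dropout and arrives at 54 per group. No group size, ICC or design effect appears.

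On the analysis, Statistical analyses says: "To evaluate the effects of the intervention, longitudinal linear and logistic regression analysis will be used". The adjustments named are baseline values and possible confounders such as gender and age, with interaction terms for gender and age. In Economic evaluation, for the difference in mean total costs, "bootstrapping will be used to estimate 95% confidence intervals"; the resampling unit is not given.

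**The concern.** This is an individually randomised trial with clustering in one arm, a partially nested design. Adolescents who attend interactive sessions together, set goals, and discuss problems at boosters may come to resemble each other in behaviour, quality of life and BMIsds. Any such correlation raises the variance of the Go4it mean above what independent subjects would give, while nothing comparable is described for the control arm.

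An analysis that models only repeated measures within a person does not capture this. Its confidence intervals would be too narrow and its tests would reject too often, in either direction. The cost-effectiveness intervals and acceptability curves would look too certain for the same reason. Real power would also be lower than the calculation suggests. The comparison most exposed is the primary one, BMIsds, because its confidence interval carries the claim of effectiveness.

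**Working it through.** **Inputs from the Sample size calculation section.** Difference 0.29, SD 0.5, alpha 0.05 (sidedness not stated; two-sided assumed), power 0.80, 43 per group, 25% dropout.

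**Inputs assumed.** Group size m from 6 to 12 and ICC from 0 to 0.10. The documents give neither.

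**Step 1: the plan's own figure.** n per group = 2 × [0.5 × (1.960 + 0.842)/0.29]² = 46.66, so 47 (48 with the t distribution; 37 if one-sided). The stated 43 is not reproduced. Power at 43 per group is Φ(0.58 × √21.5 − 1.96) = Φ(0.729) = 0.767, where 0.58 = 0.29/0.5. The 54 per group is 43 × 1.25 = 53.75, rounded up; after 25% loss, 54 leaves 40.5 per group, with power of about 0.74. This is a separate error. It matters here because the baseline for the clustering calculation is 76.7%, not 80%, and the 43 contains no hidden allowance for clustering.

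**Step 2: clustering in one arm.**
- Design effect in the Go4it arm: DE = 1 + (m − 1) × ICC. Control arm: 1.
- With equal arms, true variance / naive variance = (1 + DE)/2, so the SE ratio is R = √[(1 + DE)/2].
- Type I error when the group is ignored = 2[1 − Φ(1.96/R)].
- Power of a valid test at 43 per arm ≈ Φ(0.58 × √21.5 / R − 1.96).

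**Step 3: one case in full, m = 8 and ICC 0.05.** DE = 1 + 7 × 0.05 = 1.35. R = √(2.35/2) = 1.084. Type I error = 2[1 − Φ(1.96/1.084)] = 0.071. Power = Φ(2.689/1.084 − 1.96) = 0.70.

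**Step 4: the range of type I error when groups are ignored.**

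| ICC | m = 6 | m = 8 | m = 12 |
|---|---|---|---|
| 0 | 5.0% | 5.0% | 5.0% |
| 0.01 | 5.3% | 5.4% | 5.6% |
| 0.02 | 5.6% | 5.8% | 6.3% |
| 0.05 | 6.5% | 7.1% | 8.3% |
| 0.10 | 8.0% | 9.2% | 11.5% |

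**Step 5: power and sample size at m = 8.**

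| ICC | SE ratio | Power at 43 per arm | n per arm for 80% power, before dropout |
|---|---|---|---|
| 0 | 1.000 | 76.7% | 47 |
| 0.02 | 1.034 | 74% | 50 |
| 0.05 | 1.084 | 70% | 55 |
| 0.10 | 1.162 | 64% | 63 |

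**Check by simulation.** With 40,000 simulated trials per setting, a t test that ignored groups of 8 rejected a true null in 5.0%, 7.3% and 9.3% of trials at ICC 0, 0.05 and 0.10. This agrees with the formula.

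**Limits.** The figures are for an unadjusted comparison at one time point, using normal quantiles. The planned model adjusts for baseline, so the ICC that matters is that of the adjusted outcome. At m = 8 the Go4it arm would hold about 5 to 7 groups (43/8 = 5.4; 54/8 = 6.75), so a test with small-sample degrees of freedom would have somewhat less power than shown.

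**The case against.** A reader might infer that the plan treats adolescents as independent, and hence that its standard errors are too small and its type I error is above 5%. The article does not support stating that as fact. It gives no covariance structure at all, not even for repeated measures within a person. A longitudinal regression does not exclude a group level, and the full protocol or SAP, not shown here, may specify one. The same holds for the bootstrap unit. At ICC 0 there is no inflation, whatever the group size.

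Other premises are also unstated. The article does not say that groups were closed, how many there were, or whether different therapists led them; one team leading every group would add no variance between groups from therapists. Nor does it say whether control participants shared dieticians.

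The ICC at the target time could also be small. The last booster is listed at 36 weeks. Even if that is counted from the end of the seven sessions (six intervals of 2–3 weeks, or 12–18 weeks, hence week 48–54), 18 months (about 78 weeks) falls at least 24 weeks later. A single ICC range cannot be carried over to every secondary outcome, the logistic models and the costs.

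Finally, it would be wrong to charge the whole gap between 80% and the power figures to clustering: about 3 points (80 − 76.7) come from the arithmetic error.

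All of this stands, and it makes the point conditional. It does not remove it. The sample size is a finished calculation with its inputs on show, and clustering is not among them. The analysis section names its model and adjustments, and the therapy group is not one of them.

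**Conclusion.** The point holds in conditional form. Group delivery in one arm and individual randomisation are documented. The sample size makes no allowance for within-group correlation, and neither the regression nor the bootstrap names a therapy-group level. If the ICC is positive and the analysis leaves the group out, intervals are too narrow and the type I error exceeds 5%: barely at ICC 0.01, and by 3 to 6.5 percentage points at ICC 0.10 for groups of 6 to 12. Power at 43 per arm falls by a further 3 to 13 points from its true starting value of 76.7% at m = 8 and ICC 0.02 to 0.10. These sizes rest on assumed group sizes and ICCs. The documents do not establish that inflation will occur, so this should be fixed but is not a fatal flaw.

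**What to change.** - Record the Go4it group of each intervention participant. The article does not say whether this was kept; delivery is described in the past tense, so it may have to be recovered from session records.
- At least for the primary BMIsds analysis, add a random effect for therapy group in the Go4it arm only (controls as singletons) beside the person-level effect, with Kenward-Roger or Satterthwaite degrees of freedom.
- In the economic evaluation, resample whole therapy groups in the Go4it arm where the number of groups allows. With only 5 to 7 groups, a group bootstrap is itself unreliable, and this limit should be stated.
- Restate power over a range of ICCs, starting from the correct value at ICC 0, without enrolling more patients.

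The cost is one variable, one model term and a short restatement of power. The downsides are wider intervals (SE about 3% to 16% larger at m = 8 over ICC 0.02 to 0.10) and, with few groups, a poorly estimated variance component.

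### Intention-to-treat is defined as not imputing missing data; the rule covers all analyses and leaves incomplete cost totals with no stated handling

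*Protocol article*

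**What the plan says.** Under Statistical analyses, the protocol article states: "All analyses will be performed according to the intention-to-treat-principle, meaning that we will not impute values for missing data". Nothing in that section says that all randomised participants are analysed in the arm to which they were allocated.

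The effect analysis is given in the same section: "To evaluate the effects of the intervention, longitudinal linear and logistic regression analysis will be used". It continues: "Regression analyses will be adjusted for baseline values and possible confounders such as gender and age". The Measurements section gives the visits: "Data were collected at baseline and after 6 and 18 months intervention".

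The Sample size calculation section bases its number on an intention-to-treat analysis at 18 months and adds: "A sample of 108 persons (n = 54 per group) is required taking into account a dropout rate of 25" (per cent).

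The Economic evaluation section invokes the same principle: "The economic evaluation will be performed according to the intention-to-treat principle". On the data source it says: "Relevant cost data will be collected through cost diaries". The quantities estimated are the difference in mean total costs and cost-effectiveness ratios, with bootstrap intervals. The section has no rule of its own for incomplete diaries.

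**The concern.** Intention-to-treat settles who is analysed and in which arm. Whether missing values are imputed is a different decision, and refusing to impute neither defines the principle nor achieves it. This is a rule that the article states, not a detail left for later, so an analysis plan that follows it would carry the error forward.

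Two things are at stake. The first is the label: a regression on follow-up values, adjusted for baseline, leaves out anyone with no follow-up value, yet would be reported as intention-to-treat. The second, and larger, is cost. A total cost is a sum over diaries. If a diary is missing and nothing may be imputed, the natural options are to drop the person or to understate the total. The cost difference, the ratios, the planes and the acceptability curves all rest on that total.

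Loss related to arm is plausible. By the Intervention section, one arm attends seven group sessions, four boosters and separate parental sessions, and the other is referred to a dietician.

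**Working it through.** **Inputs**

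- Randomised: 108, 54 per arm (Sample size calculation).
- Expected dropout: 25% (Sample size calculation).
- Follow-up values: 6 and 18 months (Measurements).
- Model: longitudinal regression adjusted for baseline (Statistical analyses).
- Costs: diaries, summed to a total per person (Economic evaluation).
- Not given: when dropout occurs, the number of diaries, their completion rate, and the period that costs cover.

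**The plan's own figure.** 43 × 1.25 = 53.75, rounded up to 54 per arm, 108 in all. This reproduces the stated total. (Dividing by the retained fraction gives 43 / 0.75 = 57.3, so 58. That, and the derivation of 43 itself, are separate matters and do not affect what follows.)

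**Participants without an 18-month value**

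- 0.25 × 108 = 27 missing.
- 108 − 27 = 81 observed, or 40.5 per arm.

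**Participants absent from the longitudinal BMIsds model.** With baseline as a covariate, a person needs at least one follow-up value. Let *f* be the share of dropouts who leave before month 6 (assumed, full range shown), and suppose that the others attend the 6-month visit.

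| *f* | Excluded = 27 × *f* | Analysed = 108 − 27 × *f* |
|---|---|---|
| 0 | 0 | 108 |
| 0.5 | 13.5 | 94.5 |
| 1 | 27 | 81 |

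So 27 is the upper limit of the number excluded, not the expected number.

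**Validity of what remains.** A likelihood-based mixed model that uses all available values, with nothing imputed, is valid under missing at random. Unweighted generalised estimating equations generally need data missing completely at random, apart from missingness explained by covariates in the model. The phrase longitudinal regression fits both.

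**Participants with a complete total cost.** Assume that the total runs to 18 months and that dropouts return no further diaries.

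- Upper limit: 108 − 27 = 81.
- If a further 10% of completers have an incomplete diary set (assumed): 81 × 0.90 = 72.9, about 73.
- If 30% (assumed): 81 × 0.70 = 56.7, about 57.

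**The case against.** The strongest reply is that for the primary outcome nothing need be wrong beyond the wording. The model is longitudinal, so people lost after month 6 still contribute. A likelihood-based fit needs no imputation, and someone with only a baseline value carries almost no information on the treatment effect. This stands. A reader might infer that the rule removes the whole 25% from the BMIsds analysis, or that imputing BMIsds is required. The article supports neither.

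On costs, the reply is that the no-imputation clause sits with the effect regressions, that the economic section repeats intention-to-treat without it, and that methods without imputation exist, such as inverse-probability weighting or repeated-measures cost models. This stands in part. A reader might infer that the plan commits to complete-case costs, but it never says so. What can be said is that the clause covers all analyses, that the economic section names the same principle, and that no alternative is given. A full protocol or analysis plan might leave the handling of diaries open without fault, but here a stated rule appears to close off the usual method.

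A reader might also want a figure for the bias, and the documents do not supply one. If the 25% lost in one arm alone did 0.29 BMIsds worse than completers, the completers' comparison would be off by 0.25 × 0.29 = 0.07. If dropouts differed equally in both arms at equal rates, it would be off by about 0. Both are assumed illustrations. A shift that observed data do not predict would also survive a missing-at-random model, so the 0.07 does not measure the harm of the no-imputation rule.

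**Conclusion.** The definition is wrong, and this rests on the article's own words. The consequences are narrower than the definition suggests.

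- **BMIsds:** 0 to 27 of 108 are absent from the model, depending on the timing of dropout. The analysis can be sound without imputation, provided that it is likelihood-based and missing at random is tenable.
- **Costs and cost-effectiveness:** this is the larger problem. At most about 81 of 108 would have a complete 18-month total. This assumes that the rule reaches the economic evaluation, that costs run to 18 months and that dropouts return no further diaries. That reading is the natural one but remains an inference.

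This should be fixed. It does not make the primary analysis invalid as written, and no size of bias can be derived from the documents.

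**What to change.** 1. Define intention-to-treat as all randomised participants analysed in their allocated arm, and detach the statement on imputation from it.
2. For BMIsds, specify a likelihood-based mixed model using all available 6- and 18-month values, and state the missing-at-random assumption. No imputation is needed.
3. Exempt costs and cost-effectiveness from the no-imputation rule. Use multiple imputation by arm, combined with the bootstrap already planned.
4. Add one sensitivity analysis for 18-month BMIsds that departs from missing at random, for example by shifting the values of dropouts over a stated range.

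The cost is a few sentences and modest extra programming, mainly to combine imputation with the bootstrap. No new data and no change to the sample size are needed.
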